### Data Collection and Instruments

#### Overview

This study will integrate cognitive assessments, ecological momentary assessments (EMA), standardized questionnaires, and EEG recordings to evaluate cognitive performance, emotional well-being, and neural activity across both exposure conditions. Demographic data (gender, age, and occupation) and medication taken at the day of assessment will be self-reported. Cognitive and emotional data will be collected using the nonprofit Neureka app [72], developed by the Trinity College Dublin [name] Laboratory. The app incorporates mobile technology and citizen science approaches to monitor well-being and cognition in real-world contexts. It will be used to administer baseline and follow-up assessments over an 8-week monitoring period. All data collected through Neureka will be stored and processed following the European Union General Data Protection Regulation (GDPR). Additional questionnaires, including the GHQ-12, ASRS, and other standardized clinical measures of ADHD, will be administered on paper during in-person assessments.

#### Demographic and Contextual Measures

Demographic information (age, gender, education, and medication status) will be collected via a brief self-report questionnaire at baseline. The same form will also assess participants’ contact with natural environments over the previous 2 weeks, including the frequency and approximate duration of visits to outdoor green and blue spaces and any use of VR-based nature applications. These contextual variables will be used to characterize the sample and explore whether recent nature exposure moderates acute and follow-up outcomes.

#### Cognitive Assessments

Meta Mind: a gamified metacognitive task in which participants make confidence judgments after completing a series of perceptual decisions involving dot quantity discrimination [73].

Star Racer: a gamified adaptation of the Trail Making Test [74], designed to measure cognitive flexibility and executive control through alternating visuospatial tracking and task-switching components.

#### Emotional and Psychological Measures

EMA surveys containing 17 items adapted from the Quick Inventory of Depressive Symptomatology will track real-time fluctuations in mood, anxiety, and subjective cognitive well-being over the 8 weeks.

GHQ-12 will be administered to neurotypical controls as a screening tool for psychological distress. Participants scoring above the clinical threshold (a Likert score of 15 or higher) will be excluded.

The 6-item NCI will be administered at baseline and at the final follow-up to assess participants’ perceived connection with the natural world. Scores will be used to examine whether a single exposure to real or VR-simulated nature alters nature connectedness and whether baseline NCI moderates cognitive and emotional responses.

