**Methods:**

A total of 80 adults (40 with a confirmed ADHD diagnosis and 40 neurotypical controls) will be recruited and randomly assigned to either a real nature condition or an immersive VR-simulated nature condition. After a baseline assessment, participants will complete a 20-minute seated exposure in the assigned condition while 32-channel mobile electroencephalography (EEG) is recorded. Immediately post exposure, they will complete gamified cognitive tasks assessing cognitive flexibility and metacognition, self-report measures of mood, perceived restoration, simulator sickness, and nature connectedness. ADHD symptomatology and functional impact will be assessed with standardized scales at preexposure and postexposure and at the final follow-up. Ecological momentary assessment of emotional well-being, weekly self-reports of real-world nature and VR exposure, and repeated nature connectedness ratings will be collected via a mobile app over an 8-week follow-up period to characterize the decay or maintenance of effects. EEG analyses will focus on alpha-band markers of cognitive restoration, complemented by dimensional modeling of ADHD symptoms in linear mixed-effects models. The study has been preregistered on the Open Science Framework and will be prospectively registered with the Australian New Zealand Clinical Trials Registry (ANZCTR) before enrollment of the first participant. Ethical approval has been received from the Research Ethics Committee at Sligo University Hospital.

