### Study Design

This study uses a randomized experimental design with a between-subjects factor and a within-subject repeated-measures component over an 8-week follow-up period. Participants will be randomly assigned to 1 of 2 exposure conditions: a real natural environment or an immersive VR-simulated natural environment. Cognitive performance, emotional well-being, nature connectedness, and ADHD symptomatology will be assessed both before and immediately after exposure, with additional follow-up assessments conducted over the next 8 weeks, while brain activity will be continuously recorded during the exposure session.

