### Follow-Up Assessments

Existing work on nature exposure largely falls into 2 patterns: single-session studies that examine immediate effects and multiweek intervention programs involving repeated exposure (eg, weekly 45-minute walks in nature), with follow-up data suggesting that some benefits are no longer detectable at 1-month follow-up [64]. Against this background, this study includes an extended follow-up after a single 20-minute exposure to real or VR-simulated nature, delivered via an online survey platform that sends automatic weekly reminders before each assessment to support retention and minimize participant burden.

Beyond the immediate postexposure assessment, participants complete weekly online follow-ups over an 8-week period. The primary rationale for these repeated assessments is to characterize how any acute changes in cognition and mood observed at T1 decay over time. This design allows us to estimate the short-term time course of attenuation and to explore whether the pattern of change differs between exposure modalities and between individuals with different neurocognitive profiles, including varying levels of ADHD symptoms. Such information may help to inform the scheduling and dosing of future nature-based interventions.

In addition, the extended 8-week window provides an opportunity to examine more gradual shifts in lifestyle and nature relatedness. At baseline and at follow-up, we record the frequency and duration of participants’ additional contact with real outdoor nature and VR-based nature experiences, as well as repeated measures of nature connectedness using the Nature Connection Index (NCI) [65]. These data will be used descriptively and in exploratory analyses to assess whether a single experimental session has any downstream impact on everyday nature exposure or perceived connection to nature while also helping to account for ongoing environmental input when interpreting long-term trajectories.

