Secondary outcomes include trajectories of emotional well-being assessed via weekly EMA, clinical functioning in the group with ADHD (ACOS-Self), quality of life (AAQoL), and nature connectedness (NCI). EMA scores over T0-T9 will be modeled with LMMs including fixed effects for time (treated as a continuous or categorical variable depending on fit), condition, group, and their interactions, with random intercepts for participants. ACOS-Self, AAQoL, and NCI change from T0 to T9 will be analyzed using separate LMMs with fixed effects for group, condition, and their interaction. Self-reported real-world nature and VR exposure during follow-up will be explored as time-varying covariates in additional models to probe their contribution to decay or maintenance of effects.

To incorporate a dimensional perspective, *z*-scored ASRS total and subscale scores will be included as continuous predictors in a restricted set of prespecified models [85] (eg, ASRS × condition × time interactions for alpha power and cognitive outcomes). These analyses will test whether attentional trait variation predicts sensitivity to environmental exposure across the full sample, without overparameterizing models.

Multiple-comparison control will be applied at the level of outcome families: EEG (regions of interest and key contrasts), cognitive tasks (Meta Mind and Star Racer indices), EMA trajectories, and clinical measures. Within each family, *P* values will be adjusted using false discovery rate procedures; unadjusted and adjusted values will both be reported.

Model assumptions (normality of residuals, homoscedasticity, and, where relevant, sphericity) will be checked using diagnostic plots and formal tests. If assumptions are violated, transformations or robust alternatives will be considered. Missing data will primarily be handled within the mixed-model framework under a missing-at-random assumption. In addition, sensitivity analyses will be conducted using multiple imputation and complete-case subsets (participants with data at least up to T1 and T9) to examine the impact of attrition on key inferences.

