## Discussion

This study addresses a key gap in understanding how nature, both physical and virtual, interacts with distinct neurocognitive profiles to influence cognition, well-being, and brain activity. By combining behavioral tasks, self-report and symptom measures, and mobile EEG, it is designed to test whether VR-simulated nature can reproduce the short-term cognitive and neural changes associated with real-world natural exposure and whether it does so via similar or different processes. Rather than treating VR as a straightforward substitute, the protocol explicitly compares patterns of attentional engagement, alpha-based indices of restoration, and symptom-related variability across the 2 exposure types.

Focusing on adults with ADHD is intended to add both scientific and clinical value. Scientifically, it allows examination of how environmental stimulation interacts with atypical attentional and regulatory systems, using both diagnostic group comparisons and dimensional modeling of ADHD symptom scores. Clinically, it explores whether a single, low-intensity nature-based session, real or virtual, may support attentional regulation and quality of life in a population often underserved by traditional therapeutic approaches. Including both ADHD and neurotypical participants and analyzing symptom dimensions across the full sample should help distinguish effects that are broadly shared from those that are amplified or attenuated in ADHD.

The protocol also extends current work on nature exposure by combining immediate postexposure assessments with an 8-week follow-up. Weekly online measures of mood, stress, cognitive complaints, and nature connectedness (including self-reported contact with real and VR nature) will allow us to explore how any initial benefits change over time and whether decay patterns differ by exposure condition or symptom profile. These longitudinal data are exploratory rather than confirmatory but may provide useful information for designing the frequency and “dose” of future nature-based interventions.

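### The Nature Connection Index has three incompatible schedules; the one that is analysed (T0 and T9) cannot show an immediate effect of one exposure or how it decays

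*Protocol article*

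**What the plan says.** All references are to the protocol article.

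- **Emotional and Psychological Measures:** "The 6-item NCI will be administered at baseline and at the final follow-up". The purpose follows: "Scores will be used to examine whether a single exposure to real or VR-simulated nature alters nature connectedness". Baseline scores are also to be examined as a moderator.
- **Statistical Methods:** "ACOS-Self, AAQoL, and NCI change from T0 to T9 will be analyzed using separate LMMs". The fixed effects are group, condition and their interaction. No other analysis of change in the Nature Connection Index (NCI) is given.
- **Study Design:** "Cognitive performance, emotional well-being, nature connectedness, and ADHD symptomatology will be assessed both before and immediately after exposure", with further assessments over the following 8 weeks.
- **Abstract, Methods:** the measures completed immediately after exposure include "self-report measures of mood, perceived restoration, simulator sickness, and nature connectedness". In addition, "repeated nature connectedness ratings will be collected via a mobile app over an 8-week follow-up period".
- **Discussion:** "Weekly online measures of mood, stress, cognitive complaints, and nature connectedness" are to be used to explore how initial benefits change over time.
- **Outcomes:** the NCI is a secondary outcome. It is grouped with the momentary mood surveys and weekly nature contact as repeated measures meant to describe short-term decay or change after one exposure.
- **Follow-Up Assessments:** repeated NCI measures are mentioned without a number of occasions. They are for descriptive and exploratory use, to look for gradual or downstream shifts in connection to nature.

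**The concern.** The sections assert different schedules, so this is a conflict and not a detail that the article leaves to a fuller document. Staff would most naturally follow the instrument section and analysts the Statistical Methods. Those two agree with each other, on T0 and T9.

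That pair of time points does not fit the purpose attached to it. The question is whether one short session alters connectedness, but the only post-exposure value would come at the end of follow-up. Two points so far apart cannot separate no effect from an effect that appeared and faded. A null T0 to T9 result could then be reported as showing that a single exposure leaves connectedness unchanged, with the acute response unmeasured. A T1 rating that is not taken cannot be recovered later.

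The opposite case is also a problem. If sites do collect T1 or weekly ratings, the plan has no model for them, and any analysis would be chosen after the data exist.

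**Working it through.** No sample size, power or error-rate figure enters this point. The check compares the sections and counts occasions.

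**Time scale.** Procedures defines T0 as preexposure, T1 as immediately postexposure and T2 to T9 as eight weekly follow-ups. T2 is therefore week 1, and T9 is week 9 − 1 = 8.

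**NCI occasions implied by each source**

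| Source | Occasions | Count |
|---|---|---|
| Emotional and Psychological Measures; Statistical Methods | T0, T9 | 2 |
| Study Design | T0, T1, at least one later | at least 3 |
| Abstract, Study Design and Discussion combined | T0, T1, T2 to T9 | up to 1 + 1 + 8 = 10 |

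**What each stated purpose needs, and whether T0 and T9 supply it**

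| Purpose | Needs | T0 and T9 enough? |
|---|---|---|
| Effect of a single exposure (Emotional and Psychological Measures) | A value soon after exposure | No; first post-exposure value at about 8 weeks |
| Short-term decay or change (Outcomes) | An early post-exposure value and later ones | No for decay; net 8-week change only |
| Downstream shift (Follow-Up Assessments) | A late value | Yes |
| Baseline NCI as moderator | T0 | Yes |

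**What the analysis covers.** Statistical Methods models the mood surveys over T0 to T9, but the NCI only as T0 to T9 change. Under the 10-occasion reading, 10 − 2 = 8 occasions (T1 to T8) would have no stated analysis.

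**The case against.** **Which schedule is meant.** The instrument section does not say that the NCI is given at no other time, and two other places put it immediately after exposure. Figure 1, the schedule of assessments, could not be seen here and may show the intended version. A reader might infer that the acute effect will certainly go unmeasured; the documents do not establish that. But a figure cannot remove a conflict in the text, and if T1 is collected, the missing analysis remains.

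**T9 has a purpose.** Follow-Up Assessments wants an exploratory look at gradual change, and T0 to T9 serves it. This stands. It would be wrong to say that the two-point schedule answers nothing.

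**A null is not foreordained.** Follow-Up Assessments reports, of earlier nature-exposure work, that "some benefits are no longer detectable at 1-month follow-up", and T9 is about twice as late. A reader might infer that the NCI result must be null. The text does not say that connectedness was among the benefits that faded.

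**Season and everyday contact.** A reader might infer that change in the NCI will merely reflect spring turning to autumn. April to September is the window for running the study; each participant's interval is about 8 weeks. Randomisation within diagnostic strata should balance drift between conditions, and nature contact is recorded and explored as a time-varying covariate. Within-arm change does remain open to such influences.

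**What an added T1 can show.** Both arms receive nature, and the Discussion acknowledges that there is no nonnature control. A T0 to T1 condition × time term tests whether real and VR nature differ. It would be null if both arms rose equally, so it cannot by itself show whether exposure alters connectedness.

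**Reading of Outcomes.** The wording covers three measures jointly and allows change as well as decay. Two points can show change, but not a decay pattern.

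**Conclusion.** The point holds as a schedule contradiction with a consequence for one secondary outcome. The NCI is set at T0 and T9, before and immediately after exposure, and weekly or repeatedly over 8 weeks, in different sections of the same article. These cannot all be true.

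If the instrument and analysis sections govern, the first post-exposure value comes about 8 weeks after the session. The acute effect and short-term decay then cannot be estimated, and only the exploratory downstream question can be addressed. If the other sections govern, up to eight occasions have no stated analysis. This rests on the text alone, without Figure 1.

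The documents do not support predicting a null result or attributing any change to season. Primary outcomes, power and sample size are not affected.

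**What to change.** Settle one schedule before data collection, planned from April 2026.

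**Option A, measure the acute response.**
- Add the 6-item NCI at T1 in Emotional and Psychological Measures. If the Abstract and Discussion reflect the intention, add it to the existing weekly app surveys as well.
- In Statistical Methods, replace the T0 to T9 change model for the NCI with a repeated-measures linear mixed model over all collected times.
- Report the within-arm T0 to T1 change for whether connectedness shifts after exposure, stating that it is uncontrolled because there is no nonnature arm.
- Report condition × time for whether real and VR nature differ, and use later times for persistence.

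**Option B, keep T0 and T9.** Correct the Abstract, Study Design, Outcomes and Discussion to match. Drop the claim about the effect of a single exposure in Emotional and Psychological Measures, and limit the NCI conclusion to 8-week change.

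**Cost.** Option A adds six items at T1, where participants already complete a 20- to 30-minute assessment. If weekly ratings are wanted, T2 to T8 add 7 × 6 = 42 items, for 6 + 42 = 48 items over eight occasions. Option B costs only wording. Neither changes the sample size or the primary analyses.

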#### ADHD-Related Measures

To assess ADHD symptomatology and its functional impact, the following standardized instruments will be used:

ASRS: a widely used self-report questionnaire assessing the severity of ADHD symptoms across inattention and hyperactivity/impulsivity dimensions. All participants will complete the ASRS to enable dimensional modeling across the full sample.

Adult ADHD Quality of Life Questionnaire (AAQoL): a 29-item self-report scale measuring the impact of ADHD on quality of life across multiple domains [75]. This measure will be administered to participants in the group with ADHD.

ADHD Clinical Outcome Self-Report (ACOS-Self): a 15-item routine clinical outcome measure assessing ADHD symptoms, associated mental health challenges, and functional impairments [76]. It will also be used only with participants formally diagnosed with ADHD.

#### VR Tolerability Measures

The VRSQ will be completed immediately after the VR exposure. The VRSQ provides a brief assessment of oculomotor and disorientation symptoms related to cybersickness. In addition, participants in the VR condition will rate (1) how strongly they felt “as if really being in the forest” and (2) the overall comfort and tolerability of the VR experience on 7-point Likert scales. Together, these measures will be used to monitor participant safety, document tolerability and perceived presence of the VR condition, and, in exploratory analyses, examine whether cybersickness or low tolerability are associated with cognitive or EEG outcomes.

#### EEG Recording and Preprocessing

Neural activity will be recorded during the exposure session using a mobile 32-channel system (EMOTIV FLEX 2 Gel), which combines a research-grade amplifier with a wireless gel-based cap optimized for naturalistic and VR settings. The montage includes 32 active scalp sites (AF7, AF3, AF4, Fp1, Fp2, F1, Fz, F2, F3, F4, FC1, FCz, FC2, C1, Cz, C2, CP1, CPz, CP2, P1, Pz, P2, P7, P8, PO7, PO8, PO3, POz, PO4, O1, Oz, and O2), plus a Common Mode Sense and Driven Right Leg reference pair placed at the linked earlobes, providing high-impedance noise reduction and compatibility with standard ADHD biomarkers such as frontal-midline theta, P3, and theta/beta ratio [77-82]. Signals will be sampled at 500 Hz with a direct current to 45 Hz hardware passband. Participants’ scalps will be cleaned with alcohol wipes, and conductive gel will be applied until electrode impedance is ≤5 kΩ (absolute ceiling, 10 kΩ) with left-right symmetry within 1 kΩ for homologous pairs, to ensure stable signal-to-noise for both spectral and event-related potential (ERP) measures. Cables will be secured along the cap with Velcro, and the amplifier will be fixed at the occipital strap to minimize movement artifacts during seated exposure and tasks. This mobile configuration has been widely used in naturalistic and VR research to capture reliable spectral power and ERP components while allowing participants to remain in ecologically valid environments and enables comparable acquisition in both the outdoor forest and headset-based VR conditions.

Resting-state baselines will be collected preexposure and postexposure (T0 and T1) with 2-minute eyes-open (fixation cross) and 2-minute eyes-closed recordings while participants sit quietly, instructed to stay relaxed, minimize blinking, and avoid large movements. During the 20-minute nature or VR exposure, EEG will be recorded continuously while participants remain seated; they will be reminded that they may pause or terminate the session if they experience discomfort, and any early termination will be documented and treated as dropout for EEG analysis. Evidence from previous VR-EEG studies [83] and from our own pilot testing indicates that simultaneous use of the FLEX cap and the VR headset is safe and allows reliable signal acquisition. Nevertheless, because VR head-mounted display padding can occasionally impinge on frontal or frontopolar sites, headset fitting will follow a predefined substitution protocol: if AF3/AF4 are partially obstructed, frontal alpha asymmetry will be computed from the canonical F3/F4 pair; if Fp1/Fp2 cannot be used, priority will be given to maintaining midline integrity at Fz. For any substituted electrodes, 3D electrode positions will be digitized to allow offline correction of spatial shifts, and the midline chain Fz-Cz-Pz-Oz will be preserved in all participants for core spectral and ERP analyses.

Raw data will be exported from the proprietary EMOTIV format and converted to European Data Format/BioSemi Data Format for analysis. Offline preprocessing will be performed in EEGLAB and FieldTrip, using a 0.1 to 45 Hz finite-impulse-response band-pass filter and a 50 Hz notch filter to remove mains interference while preserving upper-beta activity relevant for theta/beta ratio outcomes. Data will then be re-referenced to the average of all scalp channels. Continuous recordings will be visually inspected to mark gross artifacts (eg, cable pops or sudden movement) and sections with poor contact. Independent component analysis will be applied to identify and remove stereotyped ocular and muscle components, following established guidelines for mobile and VR EEG. Remaining data will be segmented into 2-second nonoverlapping epochs for resting-state spectral analyses and into −200 to 800 ms epochs time locked to task stimuli or responses for ERP measures (N2/error-related negativity, P3, and related indices). Epochs showing extreme amplitudes or improbable distributions (as indexed by EEGLAB joint-probability and kurtosis metrics) will be rejected, ensuring that only artefact-free data contribute to power and ERP estimates.

To address concerns about VR-specific noise, exposure sessions will be conducted with participants seated, with head and body motion restricted to comfortable postural adjustments. Headset straps will be adjusted to avoid direct pressure on electrodes, and any pressure-related noise will be monitored online via impedance checks and offline via topographical inspection. Because the same EEG hardware, montage, and preprocessing pipeline are used in both exposure conditions, any residual artifacts linked to the outdoor environment (eg, occasional muscle adjustments due to temperature) or to the VR headset will be treated symmetrically and accounted for at the analysis stage (eg, sensitivity analyses excluding highly contaminated channels or sessions). This rigorous acquisition and preprocessing protocol is designed to ensure that observed changes in theta/beta ratio, frontal midline theta, posterior alpha power, and ERP components can be interpreted as meaningful indices of cognitive engagement and restoration rather than artifacts of the recording setup.

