### Statistical Analysis

#### Outcomes

The primary outcomes of this study will be: (1) changes in indices of neural restoration and engagement (parietal-occipital alpha power, frontal midline theta, and frontal alpha asymmetry) from preexposure to postexposure; (2) performance on two cognitive tasks: Meta Mind (confidence score, accuracy, and reaction time) to evaluate metacognition, and Star Racer (completion time, error rate, and task-switching cost) to measure cognitive flexibility and executive control; and (3) ADHD symptom severity, assessed by ASRS, included in both diagnostic group comparisons and dimensional modeling across the full sample.

Secondary outcomes will include exploratory trajectories of emotional well-being assessed through EMA, as well as self-reported nature connectedness (NCI) and weekly real-life contact with natural environments. These repeated measures are intended to characterize short-term decay or change patterns after a single exposure. Clinical change in the group with ADHD will be measured with the ACOS-Self, and quality of life with the AAQoL. Measures of VR tolerability and cybersickness (VRSQ) will be analyzed descriptively and, where appropriate, as covariates to aid interpretation of cognitive and EEG outcomes.

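### Frontal alpha asymmetry, a primary outcome, can change electrode pair in the VR arm only, so the real-versus-VR comparison of this index is not like for like

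*Protocol article*

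**What the plan says.** The Outcomes section of the protocol article lists three neural indices as primary, each as change from before to after exposure: "parietal-occipital alpha power, frontal midline theta, and frontal alpha asymmetry".

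EEG Recording and Preprocessing then sets a conditional definition for the third. It starts from the headset: "because VR head-mounted display padding can occasionally impinge on frontal or frontopolar sites, headset fitting will follow a predefined substitution protocol". The rule that follows is that "if AF3/AF4 are partially obstructed, frontal alpha asymmetry will be computed from the canonical F3/F4 pair". AF3/AF4 is never named separately as the default pair, but the rule makes sense only if it is.

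The same section lists a common 32-site montage whose frontal part reads "AF7, AF3, AF4, Fp1, Fp2, F1, Fz, F2, F3, F4", so both pairs are recorded in every participant. Three safeguards are offered:

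- Position digitizing: "For any substituted electrodes, 3D electrode positions will be digitized to allow offline correction of spatial shifts".
- A statement of common handling, which begins "Because the same EEG hardware, montage, and preprocessing pipeline are used in both exposure conditions" and concludes that residual artifacts will be treated alike in both arms.
- As an example of handling at the analysis stage, "sensitivity analyses excluding highly contaminated channels or sessions".

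Resting recordings are made before and after exposure, at T0 and T1. The text does not say whether the headset is worn for them, or whether a switched participant's T0 value is also taken from F3/F4.

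**The concern.** Under Exposure Conditions, only participants assigned to VR wear a headset. A rule triggered by headset padding can therefore apply in one randomized arm and never in the other. The forest arm stays on one electrode pair, and the VR arm becomes whatever mixture the headset fittings produce. The definition of a primary outcome then depends on the assigned condition, so a difference between conditions in this index could partly reflect which electrodes were used.

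The arm dependence is also avoidable. The fallback pair is recorded in everyone, and the protocol itself calls it the canonical pair.

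**Working it through.** **Do the stated safeguards restore a common definition?**

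- Digitizing corrects for an electrode that sits in a displaced position. It does not turn an F3/F4 value into an AF3/AF4 value.
- The statement of common hardware, montage and pipeline is true of what is recorded. The pair used to compute the index is a separate choice, and that choice is not common to the arms.
- The sensitivity analyses remove contaminated channels or sessions. They do not put all participants on one pair.
- The midline chain Fz-Cz-Pz-Oz is preserved in all participants, but an asymmetry index needs a left-right pair.

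None of the four removes the arm dependence.

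**How large could the effect be?** The plan gives no figure to reproduce. Let A be the AF3/AF4 value, F the F3/F4 value, δ the mean of F − A at a fixed time, and p the share of VR participants switched. There are 40 participants per condition (Power section: 20 per subgroup, two diagnostic groups).

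*Case 1: a switched participant has T0 from AF3/AF4 and T1 from F3/F4.* The change score is F1 − A0 = (F1 − F0) + (F0 − A0), so the whole offset δ enters. The spurious difference between arms is p × δ.

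*Case 2: a switched participant has both values from F3/F4.* The change score is F1 − F0, and δ cancels. With c_F and c_A the mean changes on the two pairs, the arm difference due to the pair is p × (c_F − c_A). This is zero if neither pair changes. Scale and noise may still differ between arms.

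The document gives neither p (the padding is said to impinge only occasionally) nor δ, so both are assumptions. For Case 1, with δ in SDs of the change score, the table gives p × δ and the simulated rejection rate when there is no true effect (two-sample t test, 40 per condition, two-sided 0.05, 4,000 replicates, before any false-discovery adjustment):

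| Share switched p | Offset δ (SD) | p × δ (SD) | Rejection rate |
|---|---|---|---|
| 0.10 | 0.25 | 0.025 | 0.051 |
| 0.10 | 0.50 | 0.05 | 0.052 |
| 0.10 | 1.00 | 0.10 | 0.067 |
| 0.25 | 0.25 | 0.0625 | 0.060 |
| 0.25 | 0.50 | 0.125 | 0.086 |
| 0.25 | 1.00 | 0.25 | 0.188 |
| 0.50 | 0.25 | 0.125 | 0.086 |
| 0.50 | 0.50 | 0.25 | 0.195 |
| 0.50 | 1.00 | 0.50 | 0.537 |

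The rows with p = 0.50 sit poorly with the word occasionally and are upper bounds. The table does not apply to Case 2.

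**After the change.** With one pair for everyone at every time point, p = 0. Both p × δ and p × (c_F − c_A) are then zero by construction.

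**The case against.** The best defence is that the outcome is a within-person change. If each person keeps one pair at T0 and T1, a fixed offset drops out and, with no true change, no mean bias is left. The resting recordings may also be made without the headset, in which case the obstruction need not arise in the windows that matter. Both points are sound, but the text settles neither. They limit the likely size of the problem and leave the arm-dependent rule in place.

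Four stronger readings are tempting, and the documents do not support them:

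- A reader might infer that the VR arm is wholly on F3/F4 and the forest arm wholly on AF3/AF4. The rule works participant by participant, and only when padding obstructs the sites.
- A reader might infer that the trial's main real-versus-VR test is compromised. Statistical Methods names alpha power in frontal and parietal regions as the primary EEG contrast, and the Power section is built on alpha power and the cognitive tasks. The pair rule concerns the asymmetry index alone. Parietal alpha power and midline measures lie outside it.
- A reader might set the figures above against the Cohen d of 0.49 in the Power section. That value is a within-subject pre-post effect on alpha amplitude. It is a different outcome and a different contrast, so the ratio has no meaning here.
- A reader might call the symmetry statement false. It is about residual artifacts and does not address the choice of pair. It fails to cure the problem, which is a weaker charge.

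It can also be said that Statistical Methods names no contrast for asymmetry. Outcomes nevertheless lists it as primary, so it needs one definition across arms.

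**Conclusion.** The point holds, and the plan should be changed. A stated rule lets the definition of one primary EEG index vary in the VR arm only, and no stated safeguard restores a common definition. The conclusion rests on one inference, that AF3/AF4 is the default pair.

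The size of the bias cannot be fixed from the document. With pairs mixed within a person, the assumed ranges run from negligible (0.025 SD, rejection rate about 0.05) to material (0.25 SD, about 0.19, at 25% switched with an offset of 1 SD or at 50% with 0.5 SD), and higher in the extreme row. With one pair per person, the fixed offset cancels and only differences in scale, noise and pair-specific change remain. Because the effect may be small and touches one of three neural indices, this is a should-fix rather than a threat to the trial as a whole.

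**What to change.** State in EEG Recording and Preprocessing, and in Outcomes, that frontal alpha asymmetry is computed from F3/F4 for all participants, in both arms and at all time points, including any values taken during exposure. Delete the substitution rule for this outcome. Use AF3/AF4 only in a sensitivity analysis among participants with clean recordings at those sites. In the VR arm that subset is selected after randomization, so it should be read with caution.

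The cost is about one sentence in the protocol and one setting in the EEG pipeline. No new data, equipment or participants are needed. The change should be made before outcome data are seen, since choosing the pair later would be a post hoc change to a primary outcome. It removes the difference in definition. It does not remove any headset-related noise at F3/F4 itself, for which the planned artifact checks are still needed.
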